### Data collection

#### Assessment of cognitive functioning

Participants complete a neuropsychological test battery at four of the five study time points [baseline (pre-intervention), end of chemotherapy (post-intervention/primary endpoint), 16 weeks post-chemotherapy (first follow-up), and one-year post-baseline (second follow-up)]. The battery covered attention/working memory, verbal and visual memory, executive functioning, planning and processing speed. These cognitive domains were chosen because previous studies have shown that they are sensitive to the deleterious effects of chemotherapy (46). The tests are performed in the following order: Colour Trials Test conditions 1&2 (attention), Digit Span Test (Memory and Recall), Stroop Test (Executive functioning), Digit-Symbol Substitution Task (processing speed), Rey auditory Verbal Learning Test (Verbal Learning and memory), Tower of London (planning and executive functioning), and Visual Reproduction task (visual learning and memory). To minimize the effects of practice, different testing forms are used at different time points. The scheme of Neuropsychological test battery planned to use in the study is depicted in **Table 2**.

**Table 2 T2:** Neuropsychological test battery.

Domain	Functions	Test	Source	Time Taken
Speed	Mental Speed	Digit Symbol Substitution	NIMHANS Neuropsychology Battery	5-7 minutes
Attention	Focussed Attention and Cognitive Flexibility	Colour Trails Test 1 & 2	NIMHANS Neuropsychology Battery	8-10 minutes
Executive Function/ Language	Phonemic Fluency	Controlled Oral Word Association Test	NIMHANS Neuropsychology Battery	5 minutes
	Semantic Fluency	Animals Names Test	NIMHANS Neuropsychology Battery	3 minutes
Executive Functions	Verbal Working Memory	Verbal N Back Test (1 back and 2 Back)	NIMHANS Neuropsychology Battery	5-7 minutes
	Response Inhibition	Stroop Test	NIMHANS Neuropsychology Battery	10-12 minutes
Visuo-Spatial	Visuo-Spatial Construction	Rey Complex Figure Test	NIMHANS Neuropsychology Battery	10-15 minutes
Learning and Memory	Visual Memory	Rey Complex Figure Test		
	Verbal Memory	Rey Auditory Verbal Learning Test	NIMHANS Neuropsychology Battery	15 minutes
Language	Speed Reading	Comprehension

Justification: In order to assess Cognitive functions, we will use both self-report instruments to assess cognitive impairment and also evaluate cognitive functions through a task performance-based tool. Earlier studies have shown problems with working memory, attention span, information processing and mental speed in breast cancer patients following six cycles of chemotherapy (47).

#### FACT Cog

Functional Assessment of Cancer Therapy Cognitive Function (FACT-Cog) is a self-report measure used to assess cognitive impairment and its effect on the patient’s quality of life. The FACT-Cog was the first patient-reported outcome measure evaluating cognitive impairment that was validated with cancer patients. It was derived from interviews with expert clinicians and oncology patient focus groups. This 37-item assessment tool allows patients to evaluate their memory, attention, concentration, language, and thinking skills. It consists of four subscales, assessing perceived Cognitive Impairments that occurred during the last seven days, on a 5- point Likert scale (from 0 “never” to 4 “several times a day”) (48) (49).

#### Heart rate variability (HRV)

The basal cardiac autonomic status will be evaluated using heart rate variability, which measures sympathetic or parasympathetic dominance. The Electrocardiogram (ECG) is recorded for 20 min, in which 5 min artefact free and resting segment will be used for analysis. Ag/AgCl solid adhesive pre-gelled electrodes (3M) will be used. The ECG will be acquired using an ambulatory ECG system (AD Instruments) at a sampling rate of 1024 Hz and will be stored for offline analysis. The data would be analysed with an advanced HRV analysis software program (LAB CHART PRO) that is inbuilt in the system.

#### Echocardiography

Echocardiography is a test that uses high-frequency sound waves (ultrasound) emitted by a transducer across the chest. The probe generates sound waves that “echo” back to the probe. These waves are transformed into images on a monitor. Echocardiography is widely available, relatively inexpensive and can assess diastolic function. Conventional echocardiography assesses structural and functional parameters, such as left ventricular (LV) ejection fraction (EF), fractional shortening (FS), as well as diameters and volumes (50, 51).

##### Serum brain-derived neurotrophic factor (BDNF)

Assessment takes place at four out of five-time points: baseline, end of chemotherapy, first follow-up, and second follow-up. 5 ml of whole blood will be collected in a heparinized tube using a vacutainer system at each time point. Then samples will be immediately centrifuged at 2500 rpm for 10-15 min. The serum will be stored at −80°C until analysis. The serum BDNF level will be quantified using an enzyme-linked immunosorbent assay (ab212166, Abcam, Cambridge, UK).

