**Methods:**

The study is a two-arm, randomized controlled trial. Women diagnosed with stage I-III breast cancer and awaiting neo-adjuvant or adjuvant chemotherapy will be recruited from a tertiary care center in Bangalore, India. Following recruitment, subjects are randomized to the intervention group (integrated yoga therapy intervention during chemotherapy) or the control group (standard care during chemotherapy). The study’s primary outcome is to measure the quality of life (cognitive domain) using European Organization for the Research and Treatment of Cancer Quality of Life Questionnaire (EORTC QLQ-C30). The other primary objectives will include cognitive functioning using neuropsychological test battery and cardiac autonomic function testing using heart rate variability. Secondary outcomes are Brain-derived neurotrophic factor (BDNF), brain function (functional MRI), Echocardiography, serum cortisol, Functional assessment of cancer therapy-cognition (FACT-Cog V3), perceived stress scale and Ryff Scales of Psychological Well-Being. Assessments take place before, during and after chemotherapy; 16-weeks post chemotherapy and 1-year post-baseline.

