##### Serum cortisol

The serum cortisol level will be estimated using an enzyme-linked immunosorbent assay (ab108665, Abcam, Cambridge, UK). Assessment takes place at four of the five study time points: baseline, end of chemotherapy, first follow-up, and second follow-up. Changes in cortisol levels were observed in earlier studies with yoga intervention in breast cancer patients (52).

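### The BDNF collection procedure (heparinized tube, immediate spin) yields plasma, but the same section calls the stored and assayed specimen serum

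*Protocol article*

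**What the plan says.** The section of the protocol article headed as serum BDNF sets out collection, processing, storage and assay in consecutive sentences. On collection: "5 ml of whole blood will be collected in a heparinized tube using a vacutainer system at each time point". On processing: "Then samples will be immediately centrifuged at 2500 rpm for 10-15 min". On storage: "The serum will be stored at −80°C until analysis". On the assay: "The serum BDNF level will be quantified using an enzyme-linked immunosorbent assay". Sampling is at four of the five study time points: baseline, end of chemotherapy, and the two follow-ups.

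The abstract's Methods paragraph lists the outcome without a specimen type: "Secondary outcomes are Brain-derived neurotrophic factor (BDNF), brain function (functional MRI), Echocardiography, serum cortisol". The fourth objective under Aims and objectives also refers to BDNF without saying serum or plasma. The next section, on cortisol, says "The serum cortisol level will be estimated using an enzyme-linked immunosorbent assay" and gives no tube or processing step.

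**The concern.** Serum and plasma are different specimens, and the tube decides which one is obtained. A heparinized tube keeps blood from clotting, and a sample spun straight away has no time to clot in any case. Two separate details of the procedure thus point to plasma, while the heading, the storage sentence and the assay sentence all say serum.

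BDNF is a secondary outcome and, with cortisol, forms the trial's fourth objective. If the tube instruction is followed, the trial will report plasma values as serum BDNF. Readers would then misread the values and could not properly set them beside serum results from other work. A second risk follows from the ambiguity. Collection runs over about a year per participant, and staff who notice the conflict may resolve it in different ways, so that the specimen at baseline is not the specimen at follow-up. A stored sample cannot be converted from one type to the other afterwards.

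**Working it through.** The plan gives no figure to reproduce here. The check is a reading of the section's sentences against each other, using only the definitions of serum and plasma.

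| Step | What the section states | Specimen implied |
|---|---|---|
| Heading | serum BDNF | serum |
| Tube | heparinized | plasma |
| Processing | immediate centrifugation, no clotting step | plasma |
| Storage at −80°C | serum | serum |
| Assay (ELISA) | serum BDNF | serum |

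1. Serum is the fluid left once blood has clotted; plasma is the fluid separated from blood that has been kept from clotting.
2. Heparin is an anticoagulant, so blood in the stated tube does not clot. The immediate spin removes any interval in which it might.
3. The supernatant is therefore plasma. The storage and assay sentences name a specimen that the two preceding sentences cannot produce.
4. No other section describes a second tube for BDNF, a clotting step, or a correction.

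Number of samples concerned:

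- Sample size estimation gives 75 per arm, so 2 × 75 = 150 participants.
- With four sampling points, the ceiling is 150 × 4 = 600 samples.
- The same section allows for attrition of up to 20%. As an illustration, suppose all of it occurs between baseline and the end of chemotherapy and none later: 150 × 0.20 = 30 are lost, 120 remain, and the count is 150 + 3 × 120 = 510.
- The legend to Figure 2 says that some assessment is optional at follow-ups. The figure is not available, so whether this applies to BDNF is unknown, and the count could be lower.

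These are counts of samples, not effect sizes. The documents give no serum–plasma difference for BDNF, and none is assumed.

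Consequence for the analysis: Sample size estimation plans ANCOVA with the respective baseline measure as covariate, and Statistical analyses plans repeated-measures ANOVA. Both treat the values at successive time points as the same measurement. With one specimen type throughout, that condition is met, whichever type it is. With a mixture unrelated to arm, the expected effect is added noise and a weaker link between baseline and follow-up values.

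**The case against.** The best reply is that this is a slip in one laboratory paragraph. The listed outcome is simply BDNF, so plasma BDNF would satisfy it, and changing a word or a tube puts matters right. Recruitment is at a single hospital, which makes divergent practice less likely than in a multicentre trial. Assessment staff are to be blinded, and nothing suggests that specimen type would differ by arm. BDNF is one of several secondary and mechanistic measures, and the primary outcome does not depend on it.

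Most of this stands, and it sets the limits of the point. It does not remove the contradiction. The article gives tube, volume, spin speed, spin time, storage temperature and assay kit, so this is not detail left to a fuller document. The word serum is used three times within the section, so it is not one stray term either.

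A reader might infer more than the text supports:

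- **That the BDNF comparison between arms is biased.** Uniform handling gives both arms the same specimen, and the randomized comparison is not distorted by that.
- **That baseline adjustment breaks down.** This would need specimens to be mixed, which is possible but nowhere stated, and mixing unrelated to arm would cost precision rather than invalidate the adjustment.
- **That the procedure contradicts the listed outcome.** The outcome list and the objective name no specimen type for BDNF; the conflict lies within the one section.
- **That serum cortisol has the same defect.** Its section gives no tube, and whether the two assays share a sample is not said.

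**Conclusion.** The section contradicts itself. Followed as written, it produces plasma and reports it as serum BDNF, for up to 600 samples before attrition. The text does not show which side is the error: the tube may be misdescribed, or plasma may be mislabelled as serum.

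The harm is to the meaning and comparability of a secondary outcome, with a possible loss of consistency over the four time points if staff settle the conflict in different ways. There is no effect on the primary outcome or the sample size, and no bias between arms under uniform handling. The conclusion rests on the definitions of serum and plasma and on the procedure being carried out as described. It is confined to the BDNF section.

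**What to change.** Reconcile the sentences by naming one specimen type and making the tube and processing match it. There are two consistent options:

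- **If serum is intended:** replace the heparinized tube with one without anticoagulant and add a clotting step before centrifugation.
- **If heparin is to stay:** name the outcome plasma BDNF in the heading and in the storage and assay sentences, and confirm that the stated assay is suitable for heparin plasma.

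In either case, state that the same specimen type is used at all four time points in both arms. If any samples have already been collected, record which tube and processing were actually used, so that the reported outcome carries the right name and specimen types are not combined.

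The cost is a different tube and a clotting interval, or a change of wording and a check of the assay. No extra visits or blood draws are needed.

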##### Serum cortisol

The serum cortisol level will be estimated using an enzyme-linked immunosorbent assay (ab108665, Abcam, Cambridge, UK). Assessment takes place at four of the five study time points: baseline, end of chemotherapy, first follow-up, and second follow-up. Changes in cortisol levels were observed in earlier studies with yoga intervention in breast cancer patients (52).

#### Functional MRI sequences

For f MRI: Each MRI scan session would consist of the image sequences listed below,

1. T2-weighted turbo spin echo sequence with TR/TE/number of excitations (NEX) =5600ms/100ms/1, field of view=220×220 mm2, slice thickness = 4mm with no interslice gap and number of slices=25.2. High-resolution T1-weighted images will be acquired using a magnetization prepared rapid acquisition gradient-echo (MPRAGE) sequence (TR = 1900 ms; TE = 2.07 ms; inversion time = 900 ms; matrix size = 256×256; FOV = 256×256 mm; inversion time = 900 msec; flip angle (FA) = 9°; slice thickness = 1 mm; number of slices = 160).3. Diffusion kurtosis imaging data will be acquired using an echo planar imaging with twice-refocused spin echo pulse sequence in the axial plane (TR = 7300 msec; TE = 138 msec; FA = 90°; matrix-size = 128 × 128; FOV = 230 × 230 mm; slice thickness = 4.5 mm; 30 slices; no interslice-gap; spatial resolution = 1.797×1.797×4.5mm; diffusion directions = 30; b values = 0, 1000, 1500 and 2000 s/mm2).4. Functional brain volumes will be acquired using an echo-planar T2* -weighted imaging sequence. Each volume consisted of 30 interleaved 5-mm thick slices without inter-slice gap (TE = 30 ms, TR = 2000 ms, FOV = 240 mm, flip angle = 90°, voxel size = 3.75× 3.75 ×5 mm3). Total scanning time was 410 seconds (205 brain volumes).5. MRS will be obtained using Point Resolved Spectroscopy sequence (PRESS) with acquisition parameters: TR/TE = 2000ms/35ms; 2048 spectral points; 1200 Hz spectral Bandwidth and 256 averages. Unsuppressed water (with 16 averages) spectra will also be acquired immediately before the water-suppressed metabolic acquisition and was used for spectral quantifications. For frontal region, a voxel of 12×12×12mm3 will be placed in the frontal region of the brain. For anterior cingulate (ACC), a voxel of 10×10×5 will be positioned in the left ACC. The resting scan will allow us to image the intrinsic connectivity pattern.

#### Quality of life as measured by self-report EORTC QLQ C30

European Organization for the Research and Treatment of Cancer-Quality of Life (EORTCQoL C30 questionnaire version 3) will be used to assess health-related quality of life (53). This 30-item questionnaire examines global health status, physical, role, emotional, cognitive, and social functioning (with high scores indicating a high quality of life) and cancer-related symptomatology. Its validity, reliability, and sensitivity in cancer patients are well established (31, 53). Assessments will be carried out at five-time points: Baseline, pre-chemotherapy, during chemotherapy, post-chemotherapy, 16-weeks post-chemotherapy and 1-year post baseline.

#### Stress as measured by self-report perceived stress scale (PSS)

The PSS is a ten item-question scale typically used to estimate perceived stress or how individuals view their current situations as stressful. The reliability (internal reliability) of the PSS instrument is robust, ranging from 0.84 to 0.86, and its validity ranges from 0.31 to 0.76 when correlated with measures of physical and mental symptoms (54). In the proposed study assessment will be carried out at all five-time points

##### Psychological wellbeing

Questionnaire Ryff developed by Carol Ryff (55) will be used to assess psychological wellbeing at all the five time points of the study (Baseline, pre-chemotherapy, during chemotherapy, post-chemotherapy, first follow-up and second follow-up). This scale measures the elements of autonomy, environmental mastery, personal growth, positive interpersonal relationships, life purpose, and self-acceptance. Furthermore, this scale has been used widely to assess psychologic wellbeing in cancer patients (56).

##### Statistical analyses

Data will be analyzed using IBM SPSS (Version 22.0 for Windows). Sociodemographic and medical characteristics will be characterized using descriptive statistics. To evaluate attrition bias, sociodemographic and medical factors at baseline will be compared between participants who completed all assessments and those who dropped out. Under the “missing at random” assumption, characteristics usually linked with attrition (e.g., age, chemotherapy duration) will be included as covariates in all analyses.

The data will be analysed for intention to treat analysis accounting for dropouts in the groups. Data will be analysed at baseline (before chemotherapy starts), after three and six cycles of chemotherapy. We will; also try to analyse six months and one-year follow-ups. A repeated measures ANOVA will be done using *post hoc* Bonferroni correction. A p-value ≤ 0.008 will be considered significant (95% confidence interval) for a 2 group assignment over three-time points (interaction effects). Secondary analyses will be carried out to determine the bivariate relationships between predictor and outcome variables. Further regression analyses will be done to understand the mediation and moderation effects if any.

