#### Sample size estimation

Considering the effect size observed, in an earlier study by Vadiraja & Rao et al. (31), with improvement in cognitive function domain of EORTC Qol-C30 between yoga and control group as 0.49 with a 95% confidence interval and 80% power, we need a sample size of 67 subjects in each arm. If attrition is within 20% through the course of the intervention, 75 subjects will be recruited in each arm. Therefore 150 consenting subjects will be randomized into each group (yoga, n=75, and controls, n=75) with an allocation ratio of 1:1. The analyses would consider a two-tailed probability of p < 0.05 as significant. This ensures that a statistical type I error (probability of detecting a false positive) is less than 5%. The analyses will involve ANCOVA using the respective baseline measure as a covariate.

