### Integrated Yoga Therapy program (IYTP)

The IYTP intervention will be given to participants along with their chemotherapy. For those in the YI group, it starts up to a week before chemotherapy begins and lasts until chemotherapy ends. The intervention is based on earlier protocols employed by the study team for breast cancer patients and found to have good patient adherence (32, 39) that they could perform these practices 5 days/week during intensive chemotherapy treatment. **Table 1** summarizes the IYTP prescription. The intervention will consist of 14 - 24 weeks (five days a week) of hospital and home-based moderate yoga therapy sessions compared with standard care alone while patients undergo chemotherapy. The practices will be taught in the hospital by a trained yoga therapist during chemotherapy and supervised online for home practices. The initial one-week yoga session will be administered in person as a one-to-one session in the hospital setup between 9 AM to 10 AM. After the patient is discharged from the hospital post their first chemotherapy cycle, they will be advised to continue yoga practice at home between 7 AM to 9 AM with a documented video and an intervention brochure outlining the instructions and benefits of yoga. Subsequently, when they come to the hospital for their following chemotherapy cycles (once every 21 days throughout their six cycles of chemotherapy), they will be refreshed with in-person yoga sessions, where necessary refinements to their practices will be made. Also, Also, their performance in yoga will be graded using the “Yoga Performance Assessment” (YPA) scale, a tool devised by Swami Vivekananda Yoga Anusandhana Samsthana (SVYASA) and Advanced Centre for Yoga (NIMHANS) for recording patient compliance to yoga practices (43).

**Table 1 T1:** Showing the list of practices.

	Practice List	Time in minutes
**1.**	**Loosening Practices SukshmaVyayama (4 minutes)**	
1.a	Neck Forward & Backward bending	1
1.b	Neck Side Bending	1
1.c	Neck Rotation – Clockwise and Anti-Clockwise	2
**2**	**Breathing Practices (3 minutes)**	
2.a	Hands In & Out Breathing	1
2.b	Shoulder Stretch Breathing	1
2.c	Ankle Stretch Breathing	1
**3.**	**Yoga Postures or Asanas (7 minutes)**	
3.a	Tadasana (Mountain Pose)	1
3.b	Ardha Kati Chakrasana (Lateral Arc pose)	2
3.c	Padahastasana (Hand to foot pose)	1
3.d	Ardha Chakrasana (Standing Backward Bend or Half wheel pose)	1
3.e	Vrikshasana (Tree pose)	1

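### The repeated measures ANOVA, run as stated, drops anyone missing a visit, so it does not deliver the promised intention-to-treat analysis; the planned covariates do not repair this.

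*Protocol article*

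**What the plan says.** The Statistical analyses section of the protocol article promises an intention-to-treat population: "The data will be analysed for intention to treat analysis accounting for dropouts in the groups". It then fixes the software, "Data will be analyzed using IBM SPSS (Version 22.0 for Windows"), the visits, "Data will be analysed at baseline (before chemotherapy starts), after three and six cycles of chemotherapy", and the model: "A repeated measures ANOVA will be done using" a Bonferroni correction. The test of interest is the group-by-time interaction over those three visits.

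Two provisions deal with missing data. Baseline characteristics of participants who complete all assessments are compared with those of dropouts. Under a missing-at-random assumption, "characteristics usually linked with attrition (e.g., age, chemotherapy duration) will be included as covariates in all analyses". The section names no imputation, mixed model or other likelihood-based method.

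Sample size estimation names a different model, ANCOVA with the baseline value as covariate. It plans for attrition of up to 20%, needs 67 evaluable per arm and recruits 75 per arm.

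**The concern.** A classical repeated measures ANOVA needs a value at every time point for every participant. In the SPSS general linear model procedure, a participant with one missing visit leaves the analysis altogether. ANCOVA at a single visit likewise drops anyone without that outcome. The named models therefore analyse complete cases unless something is done first to the missing values, and the section describes nothing of that kind.

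The stated covariate adjustment addresses a different problem. It conditions on characteristics of the people who remain. It does not return the people who left, and it does not use the after-three-cycles score of someone who leaves before cycle six. That score is the observed information most likely to carry a missing-at-random argument.

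What is at stake is precision, and possibly bias, in the primary comparison. Arm-specific dropout is plausible here: the Limitations section accepts that participants cannot be blinded, and only one arm is asked to practise five days a week.

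A second question concerns one of the example covariates, chemotherapy duration. Randomization follows the baseline assessment and precedes chemotherapy. If duration means what was received, it is a post-randomization variable that the intervention could influence and that is cut short for those who stop early. Adjusting every analysis for it could then distort the treatment effect.

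**Working it through.** **1. The protocol's own sample size.** Inputs from Sample size estimation: standardized effect 0.49, two-sided alpha 0.05, power 80%.

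n per arm = 2(1.960 + 0.842)² / 0.49² = 2 × 7.85 / 0.2401 = 65.4, so 66. With the t distribution the result is 66.35, so 67. The stated 67 reproduces.

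**2. Complete cases at the planned ceiling.** 75 × (1 − 0.20) = 60 per arm, or 30 of 150 randomized excluded. This is 7 per arm below 67.

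Power, treated as a simple two-group contrast: Φ(0.49 × √(60/2) − 1.960) = Φ(2.684 − 1.960) = Φ(0.724) = 0.77. The t-test version gives 0.76.

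Two neighbouring issues make this worse but are separate from this point:
- 20% attrition on 67 needs 67/0.80 = 83.75, so 84 per arm, not 75.
- At the p ≤ 0.008 threshold of the Statistical analyses section, power with 60 per arm is about 0.50.

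**3. Can complete-case analysis bias the contrast?** This is an illustration, and the assumptions are mine, not the protocol's:
- three visits with unit variances;
- true effect 0.49 at the end and 0.245 at mid-chemotherapy;
- 20% missing the final visit in each arm;
- dropout in controls driven by a low mid-chemotherapy score (logistic slope 0.5 to 1.5), and random in the yoga arm.

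| Completers' contrast | Truth | Equal correlations (0.5 or 0.7) | Mid-end 0.7, baseline correlations 0.4 |
|---|---|---|---|
| Baseline to end (part of the ANOVA interaction) | 0.49 | about 0.49 | about 0.43 to 0.47 |
| Baseline to mid (part of the ANOVA interaction) | 0.245 | about 0.13 to 0.22 | about 0.11 to 0.19 |
| Baseline-adjusted ANCOVA at end | 0.49 | about 0.43 to 0.47 | about 0.37 to 0.44 |

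The unequal-correlation result for baseline to end is an attenuation of about 5% to 13% (0.49 × 0.95 = 0.47; 0.49 × 0.87 = 0.43).

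- If selective dropout is in the yoga arm instead, the direction reverses. With correlation 0.5 and slopes 1 to 1.5, the unadjusted completers' difference at the end rises to 0.57 to 0.60.
- If dropout works the same way in both arms, bias almost vanishes (at most about 1% to 2%).
- An analysis that uses the mid-chemotherapy scores under missing at random returns 0.49.

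**4. Scheduled or received duration?** Inclusion criteria require a schedule of at least six cycles, so a planned duration exists at entry. The intervention section gives a length of 14 to 24 weeks, so duration varies between patients. That may reflect regimen, or delays and early stopping. Neither section, nor Statistical analyses, says which duration is the covariate.

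**The case against.** The strongest reply is that no sentence says completers only. That reading is inferred from the named method and its usual SPSS implementation. Multiple imputation followed by the named ANOVA would fit every sentence of the section, and a condensed article may leave such detail to a fuller document. This stands in part: a proven contradiction would be too strong a claim. But the article is not silent. It names a method and a missing-data remedy, and as stated the two together do not produce the population it promises.

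A reader might infer that the plan adjusts for a post-randomization variable. The text does not establish that. Duration is given only as an example beside age, directly after a sentence about baseline factors, and scheduled duration is known at entry. The point holds only conditionally.

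A reader might also take the ANCOVA attenuation, 0.43 to 0.47 against 0.49, as the bias of the planned analysis. It is not. It belongs to a completers' ANCOVA with selective dropout in one arm only. For the repeated measures interaction, the end-of-chemotherapy contrast is unbiased under equal correlations. Nothing in the protocol shows that dropout will differ in this way, and 20% is a ceiling.

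Finally, the completer-versus-dropout comparison and the explicit missing-at-random assumption deserve credit. The comparison describes attrition but does not correct for it, and it is not specified by arm.

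**Conclusion.** The point holds in this form. The models named, run as stated, exclude participants with missing visits or outcomes. That does not deliver the intention-to-treat analysis promised, and covariates do not change it. This rests on the known behaviour of the named methods and on no prior imputation, since none is mentioned.

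The certain cost is lost information: at the 20% ceiling 60 per arm remain against the 67 needed, with power about 0.76 at two-sided 0.05. Bias is a possibility only. It requires dropout that depends on earlier scores differently by arm, and its direction follows the arm affected. At end of chemotherapy the interaction contrast shows none under equal correlations and about 5% to 13% attenuation in the unequal-correlation illustration. The mid-visit contrast was biased under both patterns when dropout was selective in one arm. The chemotherapy-duration point is an ambiguity to resolve, not an established error.

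**What to change.** Make the primary analysis a likelihood-based mixed model for repeated measures (SPSS MIXED) with arm, visit, arm-by-visit and baseline score. Include all randomized participants with any post-baseline value, and take the end-of-chemotherapy contrast as primary. This is valid under the missing-at-random assumption already made, and it settles which of the two named models is primary. Multiple imputation before the named analysis is an acceptable alternative.

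The gain applies most directly to the QLQ-C30 cognitive domain, which is measured during chemotherapy. The neuropsychological battery has no mid-chemotherapy assessment, so for it the model has no earlier post-baseline score to draw on. The mixed model recovers only part of the precision lost to missing end-of-chemotherapy values, so it does not replace a correct attrition allowance.

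Restrict covariates to values fixed at randomization. If chemotherapy duration means duration received, replace it with scheduled cycles or regimen and neoadjuvant versus adjuvant setting. If it means scheduled duration, say so. Report dropout by arm as well as overall.

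The cost is revised analysis wording and slightly more programming in the same software, with no new data.
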